## APPENDIX 6. QUESTIONNAIRE FOR PROSPECTIVE STUDY PARTICIPANTS

(i.e., those who contacted the study team in response to the SM recruitment)

### 2. Prospective participant data collection sheet

1. Name of prospective participant
  - a. First name
  - b. Last name

2. What's your Twitter handle?
  - a. \_\_\_\_\_
  - b. Prefer not to disclose
3. What's your email?
4. What's your birth date
5. Are you...?
  - Female
  - Male
  - Other
  - Prefer not to disclose
6. How do you describe yourself? (check all that apply)
  - African American / Black
  - American Indian / Alaska Native
  - Asian / Pacific Islander
  - Hispanic
  - Middle Eastern
  - White
  - Other
  - Prefer not to disclose
7. What is the highest degree or level of school you have completed?
  - No schooling completed
  - Nursery school to 8th grade
  - Some high school, no diploma
  - High school graduate, diploma or the equivalent (for example: GED)
  - Some college credit, no degree
  - Trade/technical/vocational training
  - Associate degree
  - Bachelor's degree
  - Master's degree
  - Professional degree
  - Doctorate degree
  - Prefer not to disclose
8. Did you respond to the social media recruitment message because you would like to learn more about a clinical trial?
  - a. Yes
  - b. No
9. Are you gathering information for yourself or on behalf of someone else?
  - a. For myself
  - b. On behalf of someone else

10. How helpful would you say is it when research institutions reach out directly to potential clinical trial participants via Twitter?
  - a. Very helpful
  - b. Helpful
  - c. Somewhat helpful
  - d. Not helpful at all
  - e. Don't know
11. How concerned are you about researchers and research institutions monitoring Twitter conversations to identify and contact potential study participants for clinical trials?
  - a. Very concerned
  - b. Somewhat concerned
  - c. Not too concerned
  - d. Not concerned at all
  - e. Don't know
12. When were you diagnosed with cancer?
13. Do you have active cancer? (Only if yes triage to USC Norris team)
  - a. Is it visible on scans (CT, MRI)?
  - b. Are you on active treatment?
14. Are you able to do activities of daily life independently? (e.g., eating, drinking, bathing)
15. Do you have a copy of your medical records?
16. Are you currently a patient at
  - a. USC Norris Comprehensive Cancer Center, or
  - b. USC Keck Medical Center, or
  - c. LA County USC?
17. Any other comments you want to share (free text)

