| Primary outcomes                                      | 1. Feasibility : Acceptance of and satisfaction with SM recruitment method among USC Norris study team members and Twitter users in LA County, number of cancer trials eligible to be enrolled in study, number of cancer disease types and studies that can be monitored for on Twitter simultaneously by the SC CTSI study team, time and effort it takes the SC CTSI and USC Norris team members to respond to the resulting inquiries and decide whether or not to bring the patient in for screening, eligibility rate of prospective participants, demographic and ethnic diversity rate of those who consented/enrolled, social media message click rate, website contact form usage rate.
2. Impact : Monthly observed recruitment rate vs. monthly projected accrual target by trial disease group compared to historic data. Effect size estimate of the number of people to enroll cancer trials as a result of targeted social media listening and recruitment (SML) via Twitter.                                                                                                                                                                                                                                                                                                                                                                                                                                                                                                                                                                                            |

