- Post-qualitative interviews with study team members will be undertaken to explore trial participants' views and experiences of the trial methods and intervention (principal investigators, clinical research coordinators, recruitment specialists). The interview guide is under development and will be submitted to the USC HSCIRB for review. Qualitative research expert [name] (consultant on this project) will advise this part of the study. We will gather a range of data. Please see **Table 3** that lists all outcomes in the *Data analysis* section 3.3.7.

Recruitment of USC Norris clinical trial team members: As we enroll cancer clinical trials in this study, the study co-PI ([name]) will contact the cancer trial PI via email (using USC's email system) to invite the PI and one additional study member (e.g., clinical research coordinator, recruitment specialist) to participate in an interview.

- Brief survey interviews with contacted Twitter users will be conducted by the study teams with prospective study participants who contacted the study team in response to SM recruitment. The goal of the survey is to collect demographic information about the prospective study participants and to better understand their perception of the SM recruitment method used. Qualitative research expert [name] (consultant on this project) will also advise this part of the study. (See **Appendix 6** for the full questionnaire)

Additionally, we will look at the impact of the SM intervention measured by monthly observed recruitment rate vs. monthly projected accrual target. We will calculate the effect size estimate of the number of people to enroll cancer trials as a result of targeted social media listening and recruitment (SML) via Twitter.

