|--------------------------------------|----------------------------------------------------------------------------------------------------------------------------------------------------------------------------------------------------------------------------------------------------------------------------------------------------------------------------------------------------------------------------------------------------------------------------------------------------------------------------------------------------------------|
| trial participants                   | who spoke with the study team)                                                                                                                                                                                                                                                                                                                                                                                                                                                                                 |
| Diversity of enrolled participants   | Number of people of a specific racial/ethnic background enrolled per month/number of all people enrolled per month                                                                                                                                                                                                                                                                                                                                                                                             |
| Message click rate                   | Number of times a message link was clicked/Number of message impressions                                                                                                                                                                                                                                                                                                                                                                                                                                       |

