| Contact data      | last_name            | Text             | Contact's last name                                             |                                                                                                                                        |            |
| Contact data      | gender               | Numeric          | Gender                                                          | 1=Male 2=Female                                                                                                                        |            |
| Contact data      | race/ethnicity       | Numeric          | Race/ethnicity                                                  | 1=African American / Black
2=American Indian / Alaska Native 3=Asian / Pacific Islander 4=Hispanic 5=Middle Eastern 6=White 7=Other |            |

|              |                       |         |                                                                                                                                                                              |                                                                                                                                                                                                                                                                                                                                                                     |                                                                                                |
|--------------|-----------------------|---------|------------------------------------------------------------------------------------------------------------------------------------------------------------------------------|---------------------------------------------------------------------------------------------------------------------------------------------------------------------------------------------------------------------------------------------------------------------------------------------------------------------------------------------------------------------|------------------------------------------------------------------------------------------------|

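### Race/ethnicity is collected as a multi-select item with a refusal option, but the data dictionary holds one code from 1 to 7, so the Table 3 diversity outcome cannot represent multiple or declined answers

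*Protocol*

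**What the plan says.** The questionnaire in Appendix 6 (Prospective participant data collection sheet) puts race/ethnicity in Q6 as "How do you describe yourself? (check all that apply". It lists seven categories and then "Prefer not to disclose". The same refusal option closes Q5 (gender, which also offers Female, Male and Other) and Q7 (education).

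The data dictionary in Appendix 5 has one race/ethnicity row, typed as numeric, whose value labels run from 1 to 7 and end "3=Asian / Pacific Islander 4=Hispanic 5=Middle Eastern 6=White 7=Other". Gender is coded "1=Male 2=Female". Education is coded 1 to 11, ending at the doctorate. None of the three rows has a non-disclosure code.

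Table 3 lists diversity of enrolled participants under the primary outcome measures and defines it as "Number of people of a specific racial/ethnic background enrolled per month/number of all people enrolled per month". The primary outcomes in the synopsis use a broader phrase, "demographic and ethnic diversity rate of those who consented/enrolled". Section 3.3.1 makes the Appendix 6 survey the source of these data: "The goal of the survey is to collect demographic information about the prospective study participants".

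**The concern.** The form and the dictionary describe the same item in two structures that do not fit together. The form can return several answers or a refusal. The dictionary field can hold one category and nothing else. Someone has to reduce the one to the other, and the protocol does not say how.

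This matters because of what the item is used for. Racial/ethnic diversity is a listed primary outcome. Table 4 also makes tracking it the answer to possible bias in online recruitment, with a promise to adjust the strategy if needed. Section 3.3.7 further plans patient characteristics as possible covariates. If the share of a group depends on which of two ticked boxes is kept, the measure is less useful for all of these.

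The loss may also be hard to undo. If only the single code is kept, no dictionary field preserves the other ticks, and Section 3.3.6 has identifiers deleted after at most one year.

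**Working it through.** The protocol states no figure on this point, so there is none to reproduce. The check sets the form beside the dictionary.

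| Item | Answers offered (Appendix 6) | Codes available (Appendix 5) | Answers without a code |
|---|---|---|---|
| Race/ethnicity (Q6) | 8, several allowed | 7, one value | 8 − 7 = 1 (refusal), plus every multiple answer |
| Gender (Q5) | 4 | 2 | 4 − 2 = 2 (Other; refusal) |
| Education (Q7) | 12 | 11 | 12 − 11 = 1 (refusal) |

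The two opinion items (helpfulness, concern) do carry a code 5 for a don't-know answer in Appendix 5. The dictionary therefore codes non-substantive answers in some rows and not in these three.

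**Multiple answers.** Take a person who ticks Hispanic and White. The relevant codes are "4=Hispanic 5=Middle Eastern 6=White 7=Other", and only one can be entered. With code 4 the White numerator is one short; with code 6 the Hispanic numerator is one short. With n people enrolled in the month, the share of the dropped category is too low by 1/n. The retained category is right.

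**Declined answers.** Table 3 divides by all people enrolled, so a person who declines stays in the denominator and enters no numerator. That is workable, but with no code a blank cannot be told apart from a question that was not asked or not recorded.

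**Scale of one affected person.** As an assumption, set monthly enrolment equal to the minimum figures in Section 3.3.3 (2, 2, 3, 2, 1 and 1 for the six diseases):

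- Within a disease: 1/3 = 33, 1/2 = 50 or 1/1 = 100 percentage points.
- Over all six: 2 + 2 + 3 + 2 + 1 + 1 = 11, and 1/11 = 9.1 percentage points.

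This is the effect per affected person in a monthly share. The expected error would also need the rate of multiple and declined answers, which the protocol does not give.

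**Effect of counting every tick.** With 11 enrolled, 10 single answers and one double answer, the category percentages sum to 12/11 = 109.1%. This is the price of the fix proposed below.

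**The case against.** The best case against the point is that the dictionary is not a database specification. It types two disease fields as text while giving them numeric codes, it types dates as numeric, and it has no rows for several questionnaire items. The REDCap build is not shown and may well use checkbox fields. Collapsing race/ethnicity answers is routine data management, and diversity is a descriptive feasibility measure in a pilot, with no test or threshold resting on it.

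Much of this limits how strongly the point can be put, but it does not remove it. Sections 3.3.5 and 3.3.7 present the dictionary as the complete set of success metrics. The field it states cannot hold answers that the form in the next appendix invites. That is a conflict between two stated structures, which is more than detail left for later.

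Several stronger readings are tempting and are not supported:

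- That refusals will be recorded as Other. No text says so; a blank is equally consistent with the dictionary.
- That the denominator is undefined or should be restricted to those who disclose. Table 3 fixes it as all people enrolled.
- That the gender gap corrupts the Table 3 measure. That formula is racial/ethnic only.
- That age is not captured. Appendix 5 has no row for it, but Appendix 6 asks birth date and Section 3.3.6 says age is collected and stored.
- That the diversity outcome as a whole will be wrong, or wrong by a known number of points. Any worked share for a given mix of enrolees would be hypothetical.

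**Conclusion.** The mismatch is real and should be corrected before data entry. As the appendices stand, enrolees who tick more than one race/ethnicity category would be forced into one group, and those who decline have no code. This distorts the Table 3 racial/ethnic diversity outcome for those people only. A person who ticks one category, including Other, is coded correctly.

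The size of the error cannot be estimated from the protocol. At the assumed enrolment figures, one person with a dropped category shifts a monthly share by about 9 points over all diseases and by 33 to 100 points within one disease. How many such people there will be is unknown.

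The gender and education gaps are of the same kind but bear only on the demographic diversity in the synopsis, for which no formula is given. The conclusion assumes that the data will be stored as Appendix 5 describes; if the REDCap build already uses checkbox fields, the remedy is to correct Appendix 5 to match.

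**What to change.** In Appendix 5, replace the single race/ethnicity code with seven 0/1 fields, one per category, and an eighth for non-disclosure. Add gender codes for Other and for non-disclosure, and an education code for non-disclosure.

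In Table 3, state that a person is counted in each category ticked, keep the denominator of all people enrolled, and report non-disclosure as its own row. The numerator as now worded does not require exclusive categories, so this clarifies the definition without changing it.

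The cost is a few fields before launch. Category percentages may sum to more than 100%, which a table footnote can explain.
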